## Abstract

Reducing exposure to cigarette smoke is an imperative for public health and for diabetic patients. Patients with diabetes who continue to smoke face challenges at quitting and the delivery of effective smoking cessation interventions is a major unmet need. The high-affinity α4β2 nicotinic acetylcholine receptor partial agonist varenicline in combination with counseling is effective for smoking cessation, but evidence in patients with diabetes is limited. A clinical trial of varenicline targeted specifically at smokers with T2DM is warranted. This randomized, double blind, placebo-controlled trial will be the first study to test efficacy and safety of varenicline in smokers with type 2 diabetes mellitus (T2DM) over the course of 52 weeks. We hypothesize that varenicline treatment (1 mg BID, administered for 12 weeks) would increase quit rates, maintain smoking abstinence up to 1 year after treatment, and be well-tolerated in T2DM smokers intending to quit. Efficacy end points will include carbon monoxide–confirmed continuous abstinence rate (CAR) and 7-day point prevalence of abstinence. The results of this RCT will help inform medical/health authorities and physicians worldwide whether an optimally varenicline-treated cohort of T2DM patients who smoke will experience significant success rates, without significant side effects.

Trial registration NCT01387425 (https://clinicaltrials.gov/ct2/show/NCT01387425).

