### Study outcome measures

This study is intended to compare 12 weeks treatment with varenicline to matched placebo for safety and 12–52 weeks for smoking cessation efficacy in diabetic smokers.

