#### Safety end points

A summary table will present the number of events (includes lab data), number of subjects and severity of adverse events (AEs), and serious adverse events (SAEs). Any events documented in the period from the point of treatment initiation until 1 week after randomized treatment has been discontinued (V14) will be considered as relevant to the analysis.

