#### Methods of analyses

Baseline and demographic data will be listed for all treatment groups. Summary statistics will be provided for each treatment group. At baseline, differences between varenicline and placebo groups will be evaluated by means of one-way analysis of variance and Mann–Whitney *U*-test for normally and not normally distributed continuous variables, respectively; *χ*^2^ test will be used for categorical variables. The secondary endpoints will be analyzed using procedures similar to that described above for the primary endpoint. Intention-to-treat analysis will be adopted for efficacy evaluation, assuming that subjects lost to follow-up continued smoking.

Safety data will be summarized for both treatment groups and summary statistics provided.

Any events documented in the period from the point of treatment initiation until 1 week after randomized treatment has been discontinued (V14) will be considered as relevant to the safety analysis. AEs will be coded using MedDRA (Medical Dictionary for Regulatory Activities) and assigned grades based on NCI CTCAE (National Cancer Institute Common Terminology Criteria for Adverse Events). Between-groups comparisons for both individual and clustered AE rates will be carried out using χ^2^ testing or Fisher’s exact test, as appropriate.

Multiple logistic regression models will be built to identify independent predictors associated with CARs at week 12, week 24, and week 52.

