### Safety reporting

#### Adverse events

All observed or volunteered AEs, regardless of treatment group or suspected causal relationship to study drug, will be recorded. This includes symptoms thought to be related to withdrawal from nicotine. Events involving adverse drug reactions, illnesses with onset during the study, or exacerbations of pre-existing illnesses should be recorded. Exacerbation of the disease under study (type 2 diabetes), is defined as a manifestation (sign or symptom) of the illness that indicates a significant increase in the severity of the illness as compared to the severity noted at the start of the trial. It may include worsening or increase in severity of signs or symptoms of the illness, increase in frequency of signs and symptoms of an intermittent illness, or the appearance of a new manifestation/complication. Exacerbation of a pre-existing illness should be considered when a subject requires new or additional concomitant therapy for the treatment of that illness during the trial. In addition, clinically significant changes in physical examination findings and abnormal objective test findings (e.g., laboratory) should also be recorded as AEs. For all AEs, the investigator must pursue and obtain information adequate both to determine the outcome of the AE and to assess whether it meets the criteria for classification as a SAE. For all AEs, sufficient information should be obtained by the investigator to determine the causality of the AEs (i.e., study drug or other illness).

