## Discussion

Smoking and diabetes is a dangerous liaison and promoting smoking cessation for those with diabetes must be a top priority [8]. There is a pressing need for efficient interventions to reduce or prevent morbidity and mortality in smokers with DM. The high-affinity α4β2 nicotinic acetylcholine receptor partial agonist varenicline has been shown to to be effective for smoking cessation in smokers [19, 20], including those with cardiovascular disease [21].

COPD [22], or depression [23]However, there is very limited data about its efficacy and safety in smokers with diabetes [35], and a clinical trial of varenicline targeted specifically at smokers with T2DM is warranted to better inform medical/health authorities (FDA, EMEA) and physicians worldwide. To gather such evidence we will conduct the first randomized, double blind, placebo-controlled study of efficacy and safety of varenicline (1 mg BID) in smokers with T2DM.

The study protocol adopts a number of measures that contribute to quality of the study.

The gold standard to rigorously assess smoking cessation success in drug trials is continuous abstinence. Consistent with previous varenicline RCTs [25–27] and the Society for Research on Nicotine and Tobacco recommendations [28], we have adopted.

CAR as a robust primary efficacy end point. Although smoking abstinence will be self-reported, objective biochemical validation by measurements of exhaled carbon monoxide levels with a calibrated CO meter will be mandatory at each study visit.

The RCT study design with extended follow-up at 52 weeks will provide a robust answer to determine the safety and long-term efficacy of varenicline in T2DM. The length of the study was based on the consideration that substantial changes in the primary endpoint (CAR 12-week) could be reasonably observed early in the course of the trial. It is however likely that a much longer follow-up period is necessary to firmly establish findings consistency over time, hence study duration is extended to 52 weeks. Clearly, randomization will equalize variation in smoking history and other variables between study arms, thus ensuring high quality data.

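### The Abstract and Discussion claim safety over 52 weeks, but the adverse-event comparison closes at week 13 and Table 1 schedules adverse-event collection only to week 12

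*Protocol article*

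**What the plan says.** Two places attach the 52-week horizon to safety. The Abstract describes the trial as the first to "test efficacy and safety of varenicline in smokers with type 2 diabetes mellitus (T2DM) over the course of 52 weeks". The Discussion says: "The RCT study design with extended follow-up at 52 weeks will provide a robust answer to determine the safety and long-term efficacy of varenicline".

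The operative sections set a shorter horizon:

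- **Study outcome measures:** the study is intended to "compare 12 weeks treatment with varenicline to matched placebo for safety and 12–52 weeks for smoking cessation efficacy in diabetic smokers".
- **Safety end points and Methods of analyses:** both give the same window. In the latter, events from treatment initiation "until 1 week after randomized treatment has been discontinued (V14) will be considered as relevant to the safety analysis".
- **Table 1:** the adverse-event row is marked at V1 to V5, V7, V9, V11 and V13, and is blank from V14 to V18.
- **Follow-up study visits 14 to 18:** the listed assessments do not include AEs.

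The section on adverse events counts exacerbation of T2DM as an AE, judged against severity at the start of the trial. It adds: "Exacerbation of a pre-existing illness should be considered when a subject requires new or additional concomitant therapy" for that illness during the trial. Table 1 schedules antidiabetic drug use at every visit where AEs are marked and also at V14, V15 and V18 (weeks 13, 24 and 52).

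**The concern.** A reader of the Abstract and Discussion will expect a comparison of harms between arms over a year. The methods provide one for about a quarter of that time. The article says the results are meant to inform health authorities and physicians about tolerability in patients with T2DM, so the stated horizon of the safety evidence matters. If the claim is carried into the results paper, an AE analysis to week 13 could be read as one-year safety evidence.

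The mismatch is sharpest for worsening diabetes. The definition of an exacerbation runs for the whole trial, while the AE analysis window does not. A participant who first needs additional antidiabetic therapy around week 24 or 52 would meet the protocol's own trigger for considering an exacerbation, yet would not be counted in the AE comparison.

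A smaller inconsistency sits inside the window itself: it closes at V14, a visit for which Table 1 marks no AE collection.

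**Working it through.** No sample-size or power figure is involved. The check sets the stated horizons side by side and reads the visit marks in Table 1.

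**Horizons**

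| Source | Safety horizon |
|---|---|
| Abstract | 52 weeks |
| Discussion | answered by the 52-week follow-up |
| Study outcome measures | 12 weeks of treatment; the later period is assigned to efficacy |
| Safety end points; Methods of analyses | start of treatment to 1 week after it is discontinued (V14, week 13) |
| Table 1, adverse-event row | baseline to week 12 (V13) |

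**Table 1 marks across the 19 visit columns**

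- Adverse events: 9 visits, the last at week 12. None of the 5 visits from V14 to V18 is marked.
- Antidiabetic drug use: 12 visits, namely those same 9 plus weeks 13, 24 and 52.
- Diabetic laboratory tests: baseline and weeks 13, 24 and 52.

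**Size of the gap**

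- Analysis window as a share of the claimed period: 13 / 52 = 25%.
- Outside the window: 52 − 13 = 39 weeks; 39 / 52 = 75%.
- Scheduled AE collection: 12 / 52 = 23%.

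**What is available after week 13**

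1. Secondary outcome measures compare the arms on change in fasting glucose, HbA1c, insulinemia, albumin to creatinine ratio, body weight, waist, blood pressure and heart rate at weeks 24 and 52. The section on laboratory parameters also lists diabetic laboratory tests and plasma creatinine at those weeks. These are group changes, not counts of participants with an event.
2. Serious adverse events are reportable whatever the suspected cause up to 30 days after the last dose, and later only if a causal link is suspected. For a participant who completes treatment, 30 / 7 = 4.3 weeks, so unconditional reporting ends at about week 12 + 4.3 = 16.3. After that, reporting depends on the investigator's causality judgement.
3. The section on adverse events gives no end date for recording AEs. Some late events may therefore be on record, but the analysis window excludes them.

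None of the three is a between-arm AE comparison for weeks 13 to 52.

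**Who could contribute later data**

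Only participants who complete the week-12 visit enter follow-up. The Results section gives 194 of 300 completing week 52: 194 / 300 = 64.7% (100 / 150 = 66.7% on varenicline, 94 / 150 = 62.7% on placebo).

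**The case against.** The strongest reply is that the operative text is coherent. The outcome section states the 12-week safety comparison openly, and the two analysis passages agree on treatment plus one week. A treatment-period AE window is a legitimate choice. On this view, the 52 weeks in the Abstract is only the length of the trial, and in the Discussion the word long-term belongs to efficacy. Part of this stands: the window is not an error, and no outcome or analysis section promises AE tables to week 52. It does not clear the Discussion, which credits the extended follow-up itself with answering the safety question.

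Several stronger readings are tempting but not supported:

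- **That diabetes worsening after week 13 goes unobserved.** The arms are compared on HbA1c, glucose, albumin to creatinine ratio, weight and blood pressure at weeks 24 and 52, and some late serious events are reportable. What is missing is an AE count by arm.
- **That the trial, followed as written, would report a 52-week AE result.** Following the analysis section gives AE tables that end at V14. The risk lies in the claim placed around them.
- **That antidiabetic drug use is the only post-treatment information on exacerbation.** The laboratory comparisons and serious-event reporting contradict this. Drug use does add something, because participants stay on usual care and added therapy could hold HbA1c level while the disease worsens.
- **That the lack of a stated analysis of drug use is an omission.** A statistical analysis plan not shown here may cover it.
- **That the necessary data certainly exist.** Table 1 says only that antidiabetic drug use is recorded. Nothing shows that doses or changes since baseline are captured, and the follow-up visit text does not list the item.

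**Conclusion.** The concern holds as a conflict between the stated safety horizon and the methods. The Abstract and Discussion attribute to the trial a property that its AE collection and analysis do not have: 39 of 52 weeks (75%) lie outside any between-arm AE comparison. In addition, the AE window ends at a visit with no AE collection marked.

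No endpoint, estimate or planned analysis is invalid. What changes is the conclusion on safety that the trial may draw, so the correction should be made before results are reported.

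The conclusion rests on two assumptions: that Table 1 reflects what was scheduled, and that V14 is week 13 for participants who complete treatment. For those who stop early, one week after discontinuation could fall before V14, which would shorten the window further.

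**What to change.** 1. In the Abstract and Discussion, restate the claim as AE safety during 12 weeks of treatment and one week after, in line with the outcome and analysis sections. The 52-week horizon can stay attached to efficacy and to the laboratory, weight, blood pressure and heart rate comparisons.
2. Reconcile Table 1 with the V14 window. Conduct is complete, so this means stating whether AEs were in fact asked about at V14, and whether the window for early stoppers ends one week after their own last dose or at V14.
3. Where the case report form data allow, tabulate by randomised arm the change in antidiabetic drug use since baseline at weeks 13, 24 and 52, with the number assessed at each visit. Present it as supportive information beside the HbA1c and glucose comparisons, and do not label it the only post-treatment information on diabetes worsening. If dose changes were not recorded, limit it to what was, or omit it.

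Items 1 and 2 cost a few sentences. Item 3 costs one table, conditional on the data and secondary to the restated claim. The downsides are small: the safety claim becomes narrower, and the table covers attenders only, so it is not a comparison of all 300 randomised participants.

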## Introduction

Diabetes mellitus (DM) is a condition in which high blood sugar levels persist over a prolonged period of time. The noxious effect of chronic exposure of high sugar levels on the endothelium can cause macrovascular (coronary artery disease, stroke and peripheral arterial disease) or microvascular complications (retinopathy, nephropathy, and diabetic neuropathy) in individuals with type 2 diabetes mellitus (T2DM) [1].

Given that exposure to cigarette smoke is also associated with vascular damage, endothelial cell dysfunction and clotting activation [2, 3], it is not surprising that the combined injurious effects of high blood glucose together with cigarette smoke is likely to cause the accelerated course of vascular complications as well as sexual dysfunction in diabetic patients who smoke [2–4]. Indeed, cigarette smoking has been shown to increase the risk of microvascular and macrovascular complications as well as mortality in patients with T2DM [5–8]. Consistent with these observations, quitting smoking decreases this excess risk substantially [8–10] and improves sexual health [11]. If reducing exposure to cigarette smoke is an imperative for public health, it is even more so for patients with T2DM [12].Currently approved smoking cessation medications in combination with counseling have been shown to double or triple quit rates [13, 14], but the evidence for effective cessation interventions in patients with diabetes is limited [15]. Of note, smoking prevalence in individuals with diabetes continues to be comparable to that found in the general population [16] with declines that are significantly lesser among individuals with diabetes than without diabetes [17]. Consequently, one of the major unmet needs for patients with diabetes who continue to smoke is the delivery of effective smoking cessation interventions.

The high-affinity α4β2 nicotinic acetylcholine receptor partial agonist varenicline is hypothesized to reduce craving and withdrawal symptoms by stimulating dopamine release through its agonist property and to decrease the reinforcing effects of smoking by blocking nicotine binding through its antagonist property [18]. Randomized controlled trials of varenicline (1 mg BID) administered for 12 weeks along with brief smoking cessation counseling have been shown to significantly increase quit rates in smokers with no clinically significant medical conditions [19, 20], as well as smokers with cardiovascular disease [21], chronic obstructive pulmonary disease (COPD) [22], or depression [23]. In light of its efficacy, a clinical trial of varenicline targeted specifically at smokers with T2DM is deemed warranted.

Therefore, we have designed the first randomized, double blind, placebo-controlled study of efficacy and safety of varenicline (1 mg BID, administered for 12 weeks and followed to week 52) in smokers with T2DM. We hypothesized that varenicline treatment would increase quit rates versus placebo, maintain smoking abstinence up to 1 year after treatment, and be well-tolerated among diabetic smokers.

## Methods

### Study participants

Adult smokers receiving regular treatment at diabetic outpatient clinics for T2DM will be screened for the study. To be eligible they will have to satisfy the following criteria:

#### Inclusion criteria

Type 2 diabetic patients (≤ 75 years of age, but > 18 years of age) who met the ADA diagnostic criteria [24]T2DM had been diagnosed for > 12 monthsWith 7.0% ≤ HbA1c ≤ 12.0%Regularly smoking ≥ 10 cigs/day during the past year (with no period of abstinence greater than three months in the past year)Willing to quit. This will be verified by the answer ‘‘YES’’ to both questions ‘‘Do you intend to quit in the next 30 days?’’ and ‘‘Are you interested in taking part in a smoking cessation program?’’Females of nonchildbearing potential (surgically sterilized or at least 2 years postmenopausal) who are not nursing may be included. Females of childbearing potential may be included provided that they are not pregnant, not nursing, and are practicing effective contraception.Subjects must be able to be outpatients and be assessed in a clinic setting.Participating subjects must be able to provide written informed consent.

#### Exclusion criteria

Subjects currently or within the past 12 months requiring treatment for depression. Subjects with a past or present history of panic disorder, psychosis, or bipolar disorder.Subjects with a current or recent (within the past 12 months) history of alcoholism.Subjects with a requirement to use other medications during the study that might interfere with the evaluation of the study drug (e.g., nicotine replacement therapy).Subjects with a body mass index (BMI) less than 18.5 or greater than 35.Subjects with evidence or history of clinically significant allergic (except for seasonal allergies at time of dosing), endocrine, gastrointestinal, hematological, hepatic, neurologic, pulmonary, or renal disease or a history of cancer (excluding treated basal cell carcinoma and squamous cell carcinoma). Exceptions to this exclusion may include subjects with a history of mild COPD, and stable thyroid disease.Subjects with a history of clinically significant cardiovascular disease. In addition, subjects with uncontrolled hypertension or a screening or baseline systolic blood pressure greater than 160 mm Hg or a diastolic blood pressure greater than 95 mm Hg will be excluded.

The study adheres to the ethical principles of the Declaration of Helsinki and to the International Conference on Harmonization Good Clinical Practice guidelines. The study has been reviewed and approved by the Ethical Review Board of the leading site at the Azienda Ospedaliero Universitaria “Policlinico-V. Emanuele”, Università di Catania, Italy (approval reference number: 009711) and participants will give written informed consent prior to participation in the study. The study has been registered in ClinicalTrial.gov with Trial registration ID: NCT01387425 (https://clinicaltrials.gov/ct2/show/NCT01387425).

### Study design

The study is a multicenter, double blind, placebo-controlled, randomized, clinical trial designed to assess the efficacy and safety of varenicline (1 mg BID) in comparison to placebo for smoking cessation in diabetic smokers. The duration of active treatment will be 12 weeks and participants will be followed up in the nontreatment phase for an additional 40 weeks (52 week timepoint). The study will consist of an initial screening visit followed by a total of 18 study visits (12 ambulatory visits and 6 telephone contact visits) (Fig. 1). The present protocol followed the SPIRIT guidelines (Fig. 2). The study will be conducted in 6 diabetic outpatient clinics of five Italian hospitals in the province of Catania (Italy, Sicily).

**Fig. 1 Fig1:**
[figure not shown]
Study design of a double blind placebo controlled randomized clinical trial of varenicline in diabetic smokers

**Fig. 2 Fig2:**
[figure not shown]

[figure not shown]

[figure not shown]

[figure not shown]

[figure not shown]

[figure not shown]

[figure not shown]
Spirit checklist for the study

### Study outcome measures

This study is intended to compare 12 weeks treatment with varenicline to matched placebo for safety and 12–52 weeks for smoking cessation efficacy in diabetic smokers.

#### Primary outcome measure

Consistent with previous varenicline randomized controlled trials (RCTs) [25–27] and the Society for Research on Nicotine and Tobacco recommendations [28], the primary efficacy end point is the carbon monoxide–confirmed (≤ 10 ppm) CAR from week 9 to week 24 (CAR 9–24 Wks). Smoking abstinence will be self-reported and validated by measurements of exhaled carbon monoxide levels with a calibrated handheld monitoring device (MicroCO, Vyare Medical, Inc.) during clinic visits.

